**Methods:**

The clinical effectiveness of a 2-week disease-related expressive writing procedure (writing about one's deepest thoughts and feelings regarding the experience with heart disease) compared with the standard writing task (writing about one's deepest thoughts and feelings about the most traumatic or negative event experienced in the life), a neutral writing condition (writing about the facts regarding heart disease and its treatment) and an empty control condition will be evaluated in a randomized controlled clinical trial (RCT) with repeated follow-up measurements at 3, 6 and 12 months after discharge from CR. The primary outcome is health-related quality of life (SF-12). Secondary outcome measures are depression (BDI-II), anxiety (BAI) and post-traumatic growth (PTGI). Furthermore, the study will explore the moderating effects of coping styles, type D personality, perceived emotional support and participants' evaluative ratings of the writing interventions on the main experimental effects in order to identify sub-groups of patients showing different results.

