## Methods

### Study design

A four-arm randomized controlled clinical trial with four follow-up assessments (immediately before discharge from hospital, 3 months, 6 months and 12 months after discharge) will be carried out in order to test the following primary hypotheses/outcomes: 1) a modified disease-related expressive writing intervention is effective in enhancing physical and psychological health outcomes (HRQoL, anxiety and depression symptoms, medical visits for CVD-related morbidities) relative to a sham condition in which patients write solely about the facts of their experience with CVD and relative to a control empty condition; 2) the modified disease-related expressive writing intervention is more effective in enhancing physical and psychological health outcomes than a standard expressive writing condition in which patients write about the their deepest thoughts and feelings about the most traumatic or negative event they have experienced in their life. Further hypotheses/outcomes concern post-traumatic growth and are: 1) the modified disease-related expressive writing intervention is effective in enhancing post-traumatic growth relative to sham and control conditions; 2) the modified disease-related expressive writing intervention is more effective in enhancing post-traumatic growth than the standard expressive writing task.

Secondary analyses will be conducted in order to explore the relative efficacy of the writing conditions as a function of patients' gender, age, coping styles, negative affectivity and social constraint (type D personality factors), perceived social support and evaluative ratings of the writing intervention. Accordingly, significant interactions between the experimental conditions and the moderator variables mentioned above are postulated such that, for example, patients low on avoidance will benefit more from expressive writing than avoidant patients and that patients perceiving low social support will benefit more than patients perceiving high social support.

The Medical Ethics Committee of Istituto Auxologico Italiano approved the study protocol.

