Participants will be randomized to one of the following four conditions: 1) disease-related expressive writing (DS-EW); 2) standard expressive writing (S-EW); 3) unemotional writing (Sham) and 4) an empty condition not involving a writing task (assessments only). All the active conditions (1, 2 and 3) will consist in four 20-minute writing sessions that will occur during the hospital stay within a 2-week period and that will be scheduled twice a week for each participant.

Writing instructions for the three active groups will be as follows:

At the end of the CR program and before discharge, all participants, including those assigned to the empty control condition, will be re-administered the outcome questionnaires and will be told that they will receive other follow-up questionnaires by mail at 3, 6, 9 and 12 months after discharge from hospital. A form on which to record any medical visits or events over the previous 3 months will be also sent at each participant at each follow-up assessment.

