#### Writing ratings

Immediately following the last writing session, participants will be asked to rate sixteen items reflecting some aspects of the writings and of the whole writing experience on seven-point scales from (1) not at all to (7) extremely. For example, participants will be asked to rate how emotional and how personally meaningful the essays were.

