### Statistical analysis

Data entry will be conducted by a trained research assistant who will be aware of participants' condition assignment but not of the research hypotheses. Preliminary analyses will be performed to examine assumptions for parametric statistical analysis and baseline equivalence among groups. Given the longitudinal nature of the data (repeated measurements), multilevel modeling analysis in MLwiN 2.21 (Centre for Multilevel Modeling-CMM, University of Bristol) will be used to study health outcomes (physical and mental health, anxiety, depression, post-traumatic growth and number of medical visits for cardiovascular morbidity) as functions of time and experimental conditions. This will allow testing of experimental hypothesis as cross-level interactions between slopes representing time (1^th ^level) coded as 0 for the first (immediately before discharge from hospital) follow-up, as 1 for the second (3-month) follow-up, as 2 for the third (6-month) follow-up and as 3 for the fourth (12-month) follow-up, and a categorical covariate representing conditions (2^nd ^level). We will start with a simple random intercept model (for calculating intra-class correlation [ICC]) and a simple linear growth model, followed by a model with experimental conditions as a time-invariant covariate. We then will structure more complicated models, including models with different within-individual covariance structures and models with nonlinear growth patterns. A critical alpha of 0.05 will be considered for hypothesis testing. Furthermore, on the basis of the best multilevel models structured in the primary analyses, we will explore the moderating effects of some putative covariates at level 2 such as gender, age, coping styles, negative affectivity and social inhibition (Type D personality dimensions), perceived social support and writings ratings. For these secondary explorative analyses no level of significance will be defined. Readers interested in further discussion of analyzing longitudinal data with multilevel modeling analysis are referred to an excellent guide by Kwok et al. [48] as well as a thorough treatment of the issue by Singer and Willett [49].

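### Writing ratings are planned as a moderator, although they are taken after treatment, are shaped by the assigned instructions and cannot exist in the no-writing control arm

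*Protocol article*

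**What the plan says.** The Statistical analysis section of the protocol article sets out the moderator work in one sentence: "on the basis of the best multilevel models structured in the primary analyses, we will explore the moderating effects of some putative covariates at level" (the second level, that of the patient). The list that follows includes gender, age, coping styles, "negative affectivity and social inhibition (Type D personality dimensions), perceived social support and writings ratings". The primary models to which these covariates are added carry experimental condition, with four levels, as a time-invariant covariate. No restriction to the writing arms is stated. The section adds: "For these secondary explorative analyses no level of significance will be defined".

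The purpose is given in the Abstract (Methods), where the moderators include "participants' evaluative ratings of the writing interventions on the main experimental effects in order to identify sub-groups of patients showing different results". The Study rationale calls the moderator question a second goal of the study.

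On timing, the Writing ratings section says: "Immediately following the last writing session, participants will be asked to rate sixteen items reflecting some aspects of the writings". The two examples it gives are how emotional and how personally meaningful the essays were. Under Randomization procedure and blinding, allocation follows the baseline measurements, so the ratings come after both allocation and the whole intervention. The fourth arm is described under Experimental and clinical protocol as "an empty condition not involving a writing task (assessments only".

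**The concern.** A moderator of a treatment effect describes the patient independently of treatment, and in practice it is measured before allocation. Only then does comparing arms at the same moderator value keep the protection of randomisation, and only then can a finding tell a clinician in advance who is likely to benefit.

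The writing ratings fail this on three counts: they are measured after treatment, the assigned task is expected to change them, and one arm cannot have them. If the plan is followed as written, patients in different arms are compared at equal ratings, which is no longer a randomised comparison. The analysis also covers three arms while the model it is built on has four. A reader could then take a difference between high and low raters as guidance on selecting patients, although the rating is unknown until the intervention is over.

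**Working it through.** **1. The plan's own figure.** The Sample size calculation section gives 92 patients, 23 per condition, for f = 0.4, two-sided alpha 0.05, power 0.82 and 20% dropout. A four-group one-way ANOVA with noncentrality f² × N gives, for 19 per arm (N = 76), 0.16 × 76 = 12.16 and power 0.823. Adding 20% gives 76 × 1.2 = 91.2, or 92 when rounded up to equal arms. The figure reproduces and is not disputed; 23 per arm is used below.

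**2. Timing and content, side by side.**
- Baseline questionnaires come first, then allocation, then four writing sessions within two weeks, then the ratings.
- Both expressive-writing instructions tell patients to explore their deepest emotions. The sham instruction tells them to keep to facts and leave emotions out.
- The ratings ask, among other things, how emotional the essays were. A difference between the sham arm and the expressive arms on this item is what the design intends.

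**3. Who can have a rating.**
- Three writing arms: 3 × 23 = 69 of 92, or 75%.
- Control arm: 23 of 92, or 25%, with none by design.
- If 20% dropout fell evenly and removed all follow-up, 69 × 0.8 = 55.2, about 55 patients. This is a rough guide, because a multilevel model can also use patients with partial follow-up.

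A condition-by-moderator interaction has 4 - 1 = 3 degrees of freedom with four arms and 3 - 1 = 2 with three. For the ratings, the missing one is the comparison with the empty control. Filling in a constant rating for control patients would not restore it, since a slope cannot be estimated from a constant.

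**4. Which stated contrasts are lost.** The Study design section sets disease-related writing against sham, against the empty control, and against standard expressive writing. The first and third lie within the writing arms, so an interaction with the rating can be computed. The second cannot be examined.

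**5. Illustration of the bias at a fixed rating.** The loadings and shifts here are assumptions, not protocol figures. Take two arms (A = 0 or 1) with no true effect on outcome Y and no true moderation. Let an unmeasured trait U, with variance 1, load 0.5 on both the rating R and Y. Let condition shift R by d, with within-arm variances of R and Y equal to 1.
- Within an arm, cov(R, Y) = 0.5 × 0.5 = 0.25, so the slope of Y on R is 0.25.
- Hence E(Y | A, R) = 0.25 × (R - d × A), and the coefficient of A at fixed R is -0.25 × d, although the true effect is 0.

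| Shift d (SD) | Formula, -0.25d | Simulated coefficient of A | Simulated A × R term |
|---|---|---|---|
| 0 | 0 | -0.002 | 0.005 |
| 0.5 | -0.125 | -0.131 | 0.007 |
| 1.0 | -0.250 | -0.257 | -0.001 |
| 1.5 | -0.375 | -0.375 | 0.003 |

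The simulation used 400,000 patients, so the small values in the last column are noise. The spurious effect is in the condition coefficient at a given rating. The interaction stays near zero in this model.

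**The case against.** The strongest defence is that these are secondary, exploratory analyses with no significance level. Nothing in the primary outcome, the arm comparisons or the sample size depends on them. That stands, and it limits the weight of the point. It does not make a post-treatment variable a baseline moderator or supply ratings to the control arm.

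A second defence is that the ratings remain usable for two of the three stated contrasts. This also stands: a reader might infer that the rating question cannot be examined at all, and that goes too far. What cannot be examined is the contrast with the empty control. Within the writing arms the problem is one of interpretation.

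A reader might also infer that the moderation estimates themselves would be biased. The illustration does not show this, because its interaction term stayed near zero. Other data-generating models might bias it, but that has not been demonstrated here.

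Nor can one count sixteen extra moderators from the sixteen rating items. The article does not say whether they enter singly or combined, so a total number of moderators would be a guess.

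Finally, the article already has a manipulation check by an independent rater unaware of condition. Using the ratings for that purpose overlaps with it in part, but patients' own ratings are a different source.

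**Conclusion.** The point holds, with limited consequences. As listed, the writing ratings are a post-treatment process measure labelled as a moderator. Three things follow: condition effects at a fixed rating are open to bias; moderation of the contrast with the empty control cannot be estimated, because 23 of 92 patients have no rating by design; and the ratings cannot identify patient sub-groups at entry, which is the aim stated in the Abstract.

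The first and last conclusions rest on the order of events and the writing instructions, and the second on the absence of a writing task in the control arm. The size of any bias is not known from the article. The range of 0 to about -0.37 SD depends on the assumed loadings of 0.5 and on shifts of 0 to 1.5 SD. It would be smaller where two arms rate their essays alike, as the two expressive-writing arms may. The primary comparison is unaffected.

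A separate matter is not part of this conclusion. Perceived social support is also a listed moderator, with the illustrative hypothesis that "patients perceiving low social support will benefit more than patients perceiving high social support", yet the article describes no instrument for it. A reader might infer that no such data would be collected. A condensed article does not support that, since the full protocol may name a scale.

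**What to change.** Remove writing ratings from the moderator list in the Abstract, Study rationale, Study design and Statistical analysis sections. In their place, state that the ratings will be summarised by arm within the three writing arms, either as a manipulation check alongside the independent rater's judgement or as a process measure. State also that any association with outcome is descriptive, concerns only patients who wrote, and is not evidence of who benefits from treatment.

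The cost is a few sentences and one exploratory moderator. No data collection, sample size or primary analysis changes.

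As a side request, the sponsor should confirm that a perceived social support scale is given at baseline and name it, or drop that exploratory hypothesis.

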## Discussion

For the first time the expressive writing procedure will be administered to a sample of patients with CVD referred to a 3-week residential cardiac rehabilitation program. The feasibility, safety and clinical efficacy of such a brief psychological intervention will be evaluated in a four-arm randomized controlled clinical trial with a 12-month follow-up period. Multiple psychological variables relevant to patients with CVD will be assessed in order to examine the specific effects of the expressive writing intervention on some psychosocial risk factors related to CV morbidity in this population. Furthermore, a generic measure of health-related quality of life (HRQoL) will be administered to participants at each follow-up assessment as HRQoL improvement is among the major outcomes of clinical trials [50] and was established as one of the primary goals of cardiac rehabilitation [51].

Given the novelty of the study and our will to handle a low number of outcomes, physiological data such as heart rate, blood pressure and cholesterol will not be considered for the analyses and only a measure of medical visits or events along the follow-up period will be used as a surrogate marker of bio-medical health.

This study is essentially intended to explore and expand the clinical frontiers of the expressive writing research enterprise. Altough no advancement in the theorical knowledge about the multi-level mechanisms that underlie the expressive writing task is scheduled, the results of this trial will contribute to the evidence-based knowledge on the application of the expressive writing procedure for clinical purposes in clinical settings [52].
